## Abstract

**Background:**

The recommendations outlined in the latest guidelines published by the Surgical Infection Society (SIS) and the Infectious Disease Society of America (IDSA) regarding the proper duration of antibiotic therapy in patients with intra-abdominal infections are limited and non-specific. This ambiguity is due mainly to the lack of clinical trials on the topic of optimal duration of therapy. It is well known that the overuse of antibiotics has several important consequences such as increased treatment costs, reduced clinical efficacy, and above all, the increased emergence of antibiotic-resistant pathogens. Ampicillin-Sulbactam is a commonly used "first line" antibiotic for intra-abdominal infections. Ertapenem and Ampicillin-sulbactam are recommended as primary treatment agents for localized peritonitis by both the SIS and IDSA guidelines.

**Methods/Design:**

This study is a prospective multi-center randomized investigation. The study will be performed in the Departments of General, Emergency, and Transplant Surgery of Sant'Orsola-Malpighi University Hospital in Bologna, Italy, in the General Surgery Department of the Ospedali Riuniti of Bergamo, Italy, and in the Trauma and Emergency Surgery Department of Maggiore Hospital in Bologna, Italy, and will be conducted by all surgeons willing to participate in the study. The inclusion period of the study will take approximately two years before the planned number of 142 enrolled patients is reached.

**Discussion:**

Ertapenem and Ampicillin-sulbactam are recommended both as primary treatment agents for localized peritonitis by both the SIS and IDSA guidelines. As one of the discussed topic is the optimal duration of the antibiotic therapy and this ambiguity is due mainly to the lack of clinical trials on the topic, the present study aims for obtain precise data.

**Trial Registration:**

ClinicalTrials.gov: NCT00630513

## Background

The recommendations outlined in the latest guidelines published by the Surgical Infection Society (SIS) and the Infectious Disease Society of America (IDSA) regarding the proper duration of antibiotic therapy in patients with intra-abdominal infections are limited and non-specific According to these guidelines, an "antimicrobial therapy for established infections should be continued until resolution of clinical signs of infection occurs, including normalization of temperature and WBC count and return of gastrointestinal function" [1].

Such ambiguity is primarily attributable to the lack of clinical trials conducted on the topic of the optimal duration of antibiotic therapy.

These vague guidelines have manifested themselves in clinical practice; in most trials for antibiotic therapy, a fixed period ranging from 5 to 14 days is used for all patients presenting with community-acquired intra-abdominal infection, irrespective of severity of the peritonitis.

It should be noted that secondary peritonitis encompasses several different diseases and, as such, its severity has been known vary significantly [2].

It has been demonstrated that most patients enrolled in trials involving antibiotic treatment of IAI present with a mild form of the acute illness, which in 35-55% (and, in some studies, up to 70%) of cases is represented by acute appendicitis [3]. It should also be noted that many patients do not suffer from a fully developed and widely spread infection but rather experience a localized infection or simple contamination [4].

This means that many patients receive superfluous and unnecessary antibiotic treatments. Many non-random trials demonstrated that, by tailoring the duration of the antibiotic therapy to the extent of the infection as assessed during surgery, the same clinical results could be obtained in all groups of treated patients without the use of excessive antibiotic treatment regimens [5]. A recent systematic meta-analysis of twenty-eight studies on the duration of antibiotic therapy in cases of advanced pediatric appendicitis demonstrated that limiting the duration of antibiotic use to only 3 days was not associated with higher rates of intra-abdominal abscesses or wound infection [5].

In 2006, Basoli et al. demonstrated in a randomized study that a shorter duration of Ertapenem is as effective as a standard 5-day treatment regimen in patients presenting with mild-moderate peritonitis, thereby resulting in a significant reduction in the excessive use of antibiotics. These results represent a much-needed reassessment of antibiotic treatment and a conservative shift in antibiotic regimen methodology [6].

It is well known that the overuse of antibiotics has several important consequences such as increased treatment costs, reduced clinical efficacy, and above all, the increased emergence of antibiotic-resistant pathogens. The use of excessive or otherwise inappropriate antibiotic regimens may facilitate the emergence of resistant bacterial strains [7].

The fact that Ertapenem appears to be an effective monotherapy for community-acquired IAI is particularly important.

Ertapenem is a long-term acting parenteral Group I carbapenem, which is active in vitro against most aerobic and anaerobic bacteria generally associated with community-acquired infections[8,9]. Ertapenem is not active against most *Pseudomonas aeruginosa *or enterococci, but prevention of such strains is not routinely required for successful treatment of intra-abdominal infections[10,11].

In an earlier double-blind randomized clinical trial, Ertapenem proved to be just as effective as piperacillin-tazobactam [12].

Ampicillin-sulbactam (AS) is a widely used "first line" antibiotic for treating IAI.

Ertapenem and AS are recommended as single agents for localized peritonitis in both the SIS and IDSA guidelines.

The AS daily dosage is 3 g × 3 compared to Ertapenem, which is a 1 g single administration.

In Italy, 1 g of Ertapenem costs 36 euros while 1 g of AS costs only 0.23 euros.

*Escherichia coli *is the most common bacterium involved in localized community-acquired IAI; unpublished data from a retrospective analysis of 300 cases from Sant'Orsola-Malpighi's General Surgery Department reported a growing rate of resistance of *Escherichia coli *to AS as high as 30% [13].

The aim of this study is to compare the results of Ertapenem administered in a short 3-day regimen (in terms of efficacy and safety) to a short 3-day regimen of AS for patients presenting with community-acquired IAI of mild to moderate severity.

## Methods

### Design

This study is a prospective multi-center randomized investigation. The study will be performed in the Departments of General, Emergency, and Transplant Surgery of Sant'Orsola-Malpighi University Hospital of Bologna, in the General Surgery Department of the Ospedali Riuniti of Bergamo, and in the Trauma and Emergency Surgery Department of Maggiore Hospital of Bologna, and will be conducted by all surgeons willing to participate in the study. The study has been designed and will be conducted in compliance with the regulations outlined in "Good Clinical Practice" methodology.

The efficacy of a 3-day treatment regimen of Ampicillin-Sulbactam (AS 3 g × 3/day administered intravenously) is compared to a 3-day regimen of Ertapenem (1 g/day administered intravenously) for treating patients with localized peritonitis in a blinded evaluation of established efficacy-based endpoints. Evaluation of success or failure is blinded by the use of designated third party administrators who are unaware of the treatments assigned to the patients.

### Randomization

The randomization will be achieved by means of a computer-generated assignment system (a randomization algorithm). The results of this randomization will be sealed in numbered envelopes. Following the diagnosis of localized peritonitis, if the patient meets the inclusion criteria and if he/she is willing to participate in the study, the patient will sign a document verifying informed consent at which time the attending surgeon will disclose the contents sealed within the assigned envelope to determine the patient's randomly assigned treatment group.

The attending surgeon will then record the patient name and envelope number.

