### Statistics

Each group will consist of 71 patients (142 patients for the entire study). All randomized patients (Intention to Treat Population) will be included in the analysis. Sample size has been calculated to reach a confidence level of 95% with a power of 80%. A sample size of 71 patients has been calculated assuming that Ertapenem can decrease the rate of "failure" from 30% to 10% as compared to AS.

The statistical analysis will be carried out using Epi Info 2000, Version 1.1 software package (Dean AG, Arner TG, Sangam S, Sunki GG, Friedman R, Lantinga M, Zubieta JC, Sullivan KM, Smith DC. Epi Info 2000, a database and statistics program for public health professionals for use with Windows 95, 98, NT, and 2000 computers; Centers for Disease Control and Prevention, Atlanta, Georgia, USA, 2000). The data generated in this study will be analyzed in two ways. Researchers will use the continuous numerical data to perform an analysis of variance (ANOVA), given that this method can discriminate between two continuous populations. Discrete data will be analyzed using the Chi-squared test or Fisher exact test, as appropriate. Differences between the two study groups will be considered statistically significant for p-values less than 0.05 (p < 0.05).

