### Surgical Intervention

Upon patient enrollment, the severity of the disease is evaluated by means of an APACHE II score and MPI prior to the operation. Diagnosis is based on the patient's clinical symptoms and intra-operative findings, including intra-operative cultures. The drug regimen being studied begins prior to surgery. The patients undergo surgery and then receive a 3-day treatment of either Ertapenem (1 g per day) or AS (3 g, 3× per day), depending on the assigned treatment group. Administration of the antibiotic therapy is then discontinued for those patients demonstrating an improved temperature (< 37.8°C), decreased WBC (returning to the normal range), and the presence of abdominal sounds by the third day of treatment.

In order to balance the treatment groups, the patients are stratified according to the site of infection; cases are either categorized under "complicated appendicitis" or they are filed under the all-encompassing group, "all other diagnoses." To limit the proportion of cases with complicated appendicitis, we have limited the enrollment into a stratum when almost 50% of cases are enrolled. Considering that an adequate surgical source control is a crucial factor determining the outcome of this disease, a blinded panel of three surgeons is asked to impartially assess the efficacy of the surgical procedure.

Aerobic and anaerobic cultures of intra-operatively retrieved specimens are obtained at baseline and processed in the clinical microbiology laboratories of the participating hospitals. All microorganisms are isolated, cultured, and tested for in vitro susceptibility to the study antibiotic by disk diffusion or microtiter dilution. Routine susceptibility testing of strict anaerobes is not required by treatment protocols.

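### The attending surgeon opens the envelope before recording which patient it belongs to; the order should be reversed

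*Protocol article*

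**What the plan says.** The Randomization section of the protocol article describes a computer-generated allocation: "The results of this randomization will be sealed in numbered envelopes". Once localized peritonitis is diagnosed, the patient is eligible and is willing to take part, the steps run in this order:

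1. Consent: "the patient will sign a document verifying informed consent".
2. Opening: "at which time the attending surgeon will disclose the contents sealed within the assigned envelope to determine the patient's randomly assigned treatment group".
3. Recording: "The attending surgeon will then record the patient name and envelope number".

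The Design section describes blinding for the outcome evaluation: "Evaluation of success or failure is blinded by the use of designated third party administrators who are unaware of the treatments assigned to the patients". Surgical Intervention adds a blinded panel that judges the surgical procedure. Neither provision covers the surgeon who opens the envelope.

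The Statistics section defines the analysis set by randomization: "All randomized patients (Intention to Treat Population) will be included in the analysis".

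**The concern.** A sealed envelope conceals the allocation only if the patient is committed to that envelope before anyone sees what is inside. Here the sequence is the other way round. The surgeon who handles entry to the trial reads the arm and then makes the only patient-to-envelope entry that the article describes. Between those two steps an opened envelope could be used for a different patient, or a patient could be left out of the log.

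Two things would be at stake. The first is comparability of the arms: if envelopes were used selectively by prognosis, the failure rates would differ for reasons unrelated to treatment, and blinded outcome evaluation could not correct that. The second is the analysis set. Intention to treat covers all randomized patients, so its membership should be fixed by an entry made before the arm is known.

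The setting gives the step some weight. The Design section opens the trial to every willing surgeon in departments of three hospitals, so many people may open envelopes. According to Surgical Intervention, study drug starts before surgery while diagnosis also draws on operative findings. The arm is therefore known before the diagnosis is complete.

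**Working it through.** **1. The order of steps.** The core of the point needs no arithmetic.

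| Step | What is fixed in writing | Does the surgeon know the arm? |
|---|---|---|
| Eligibility and consent | a signed consent document | no |
| Envelope opened | no further entry described | yes |
| Name and envelope number recorded | the patient-to-envelope link | yes |

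The word *then* in the last Randomization sentence places the link after disclosure. This is a stated step, not a detail on which the article is silent. That the surgeon is unblinded is an inference, but a safe one: the surgeon reads the allocation, and only the outcome evaluators are said to be unaware of it.

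**2. The plan's own figure.** The Statistics section gives 71 per group for failure rates of 30% and 10%, 95% confidence and 80% power. Sidedness is not stated; two-sided is taken.

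- Without continuity correction: n = [1.960·√(2·0.2·0.8) + 0.842·√(0.3·0.7 + 0.1·0.9)]² / 0.2² = (1.109 + 0.461)² / 0.04 ≈ 61.6, so 62.
- With continuity correction: (61.6/4)·[1 + √(1 + 4/(61.6·0.2))]² ≈ 71.2, so 72 when rounded up.

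The stated 71 is therefore reproduced to within one patient. Nothing in this point challenges it.

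**3. Illustration of size (assumed inputs only).** The documents give neither a number of misplaced patients nor a prognostic gap. Suppose k higher-risk patients in one arm are exchanged for k lower-risk patients in the other, with an assumed risk gap of 0.25. Each arm's failure rate then moves by k·0.25/71 in opposite directions, so the difference shifts by 2·k·0.25/71:

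- k = 3: 1.5/71 = 2.1 percentage points (6 of 142 patients involved)
- k = 5: 2.5/71 = 3.5 points (10 of 142)
- k = 8: 4.0/71 = 5.6 points (16 of 142)

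The planned difference is 30 − 10 = 20 points.

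**4. Illustration of the false-positive rate (assumed inputs only).** Suppose there is no true effect, 71 patients per arm, and a fraction f of each arm steered consistently by prognosis. Those patients carry r times the base risk p in one arm and 1/r of it in the other:

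p_A = (1 − f)p + f·p·r and p_B = (1 − f)p + f·p/r.

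With p = 0.20, f = 0.10 and r = 2, p_A = 0.18 + 0.04 = 0.22 and p_B = 0.18 + 0.01 = 0.19. The difference is 3 points, and a nominal two-sided 5% test rejects in about 7.3% of trials. Over f from 5% to 20% and r from 2 to 3, the rejection rate at p = 0.20 runs from about 6% to 33%. Over p from 10% to 30% it runs from about 5% to 52%. The upper ends require 20% of each arm, about 14 of 71, to be steered in one direction with a threefold risk ratio, which is an extreme case.

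**The case against.** The strongest reply is that the procedure has more safeguards than the order of two sentences suggests. Consent is signed before opening. The envelope is described as assigned, which implies use in sequence, and it carries a number. An envelope set aside would leave a gap in the numbers, and a patient dropped after opening would leave a signed consent with no matching entry. The article is a condensed account, and the full procedure may contain an earlier log entry. Recruitment is also slow: 142 patients in about two years is 142/24 ≈ 6 a month over all sites, and surgery is required within 24 hours of diagnosis. Holding an opened envelope for a suitable next patient would not be easy.

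Most of this stands, and it limits the point. It does not remove it, because none of these safeguards is a written patient-to-envelope link made before the arm is seen.

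A reader might infer more than the documents support:

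- **That there is only one envelope series, incompatible with stratification.** Randomization speaks only of numbered envelopes. Surgical Intervention says "the patients are stratified according to the site of infection". Separate series per stratum fit both statements.
- **That patients could vanish without trace, or that the intention-to-treat set cannot be audited.** Consents can be reconciled against envelope numbers. The check is partial, but it exists.
- **That surgeons have a known motive.** The resistance rate of up to 30% to ampicillin-sulbactam in the Background is unpublished retrospective data from one department, and the same section says both drugs are guideline-recommended. No document shows that surgeons prefer one arm for sicker patients. The direction of any steering is open too: sending sicker patients to ertapenem would shrink the observed difference, and the reverse would enlarge it.
- **That envelopes are translucent, used out of order or never reconciled.** The article is silent on these matters, and an article may leave them to the full protocol.

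**Conclusion.** The point holds in a narrow form. As stated, the procedure discloses the arm to the attending surgeon before any written entry ties the patient to the envelope. That is an avoidable weakness in allocation concealment and in how membership of the randomized set is fixed. It is worth correcting because the correction is almost free, not because the trial is shown to be biased.

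No size can be derived from the documents. The shifts of about 2 to 6 percentage points and the raised false-positive rates rest wholly on assumed numbers of misplaced patients, assumed risk gaps and consistent steering in one direction. They show that a modest amount of selective use could matter with 71 per arm. They are not an expected bias. The conclusion also assumes that the article reports the sequence as it is carried out. If the full protocol already requires an entry before opening, only the article's sentence is wrong.

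**What to change.** Reverse the last two steps in Randomization. After consent, the attending surgeon writes the patient identifier, date and time on the still-sealed assigned envelope, enters the same details against its number in the numbered log, and only then opens it. Add to Statistics that every patient so recorded belongs to the intention-to-treat population, whatever happens afterwards.

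The cost is two sentences of text and under a minute per patient, so less than 142 minutes (about 2.4 hours) over the whole trial. No extra staff are needed, and sample size, treatment and analysis method are unchanged. The change should be made before enrolment, or as early in it as possible: for envelopes already opened, signed consents can be reconciled with envelope numbers, but a link that was not written down before opening cannot be created afterwards.

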### Statistics

Each group will consist of 71 patients (142 patients for the entire study). All randomized patients (Intention to Treat Population) will be included in the analysis. Sample size has been calculated to reach a confidence level of 95% with a power of 80%. A sample size of 71 patients has been calculated assuming that Ertapenem can decrease the rate of "failure" from 30% to 10% as compared to AS.

The statistical analysis will be carried out using Epi Info 2000, Version 1.1 software package (Dean AG, Arner TG, Sangam S, Sunki GG, Friedman R, Lantinga M, Zubieta JC, Sullivan KM, Smith DC. Epi Info 2000, a database and statistics program for public health professionals for use with Windows 95, 98, NT, and 2000 computers; Centers for Disease Control and Prevention, Atlanta, Georgia, USA, 2000). The data generated in this study will be analyzed in two ways. Researchers will use the continuous numerical data to perform an analysis of variance (ANOVA), given that this method can discriminate between two continuous populations. Discrete data will be analyzed using the Chi-squared test or Fisher exact test, as appropriate. Differences between the two study groups will be considered statistically significant for p-values less than 0.05 (p < 0.05).

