### Data Collection

Patient data sheets are generated containing demographic figures as well as preoperative, operative, and postoperative information.

Upon enrollment, all patients undergo physical examinations and laboratory tests, (including a CBC with a WBC, differential analysis, platelet count, serum glucose assessment, BUN, and serum creatinine test). The same procedure is performed on the third day of the treatment regimen, at the end of the treatment cycle following the resolution of pathology, and during the post-treatment follow-up analysis (or more frequently as clinically relevant). Liver function studies, serum electrolytes, and urinalysis are performed upon the discontinuation of the intravenously administered antibiotic as well as periodically throughout the treatment process as clinically indicated. When clinically indicated during the course of antibiotic therapy, blood, urine and tissue specimens from clinically relevant intra-abdominal sites are obtained for culture and susceptibility testing. Such cultures are also performed at the end of antibiotic therapy, unless there is no material available for cultures and/or no clinical evidence of infection.

The clinical outcomes of eligible patients are classified in three groups: successful (no signs or symptoms of infection and no further need for antimicrobial therapy); failure (indicating no improvement, infection progression, or death due to infection); or late failure (indicating recurrence between cessation of antibiotic therapy and follow-up). Microbiological reports are recorded for each baseline pathogen. Favorable microbiological responses involve eradication of the pathogen(s), assessed on either a documented or presumptive basis (the latter occurring when there is no material available for culture in clinically recovered patients). By contrast, unfavorable microbiologic responses involve a chronic persistence of the pathogen(s), either on a documented or presumptive basis.

Any and all adverse events (AEs) that occur during the course of the study, beginning from the time of randomization, are carefully documented. These AEs are identified and described by the primary investigators.

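### The repeated laboratory panel is compared by unadjusted ANOVA although every patient has an enrolment value, and one of its visits is timed by outcome

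*Protocol article*

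**What the plan says.** The Statistics section gives one method for all continuous data: "Researchers will use the continuous numerical data to perform an analysis of variance (ANOVA"). The reason given describes a comparison of two groups, and no covariate is named. The same section states "All randomized patients (Intention to Treat Population) will be included in the analysis".

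The Data Collection section describes what is measured and when. "Upon enrollment, all patients undergo physical examinations and laboratory tests", and the tests listed include a blood count with WBC, platelets, glucose, BUN and creatinine. Then: "The same procedure is performed on the third day of the treatment regimen, at the end of the treatment cycle following the resolution of pathology", with a further round at post-treatment follow-up and extra measurements allowed ("or more frequently as clinically relevant"). Other tests have no stated enrolment value: "Liver function studies, serum electrolytes, and urinalysis are performed upon the discontinuation of the intravenously administered antibiotic".

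The same section defines one outcome class as "failure (indicating no improvement, infection progression, or death due to infection").

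The Surgical Intervention section stratifies patients as complicated appendicitis or all other diagnoses. It makes stopping of the antibiotic by day 3 depend on temperature, WBC and abdominal sounds. The Primary Endpoint section names failure rates. The Secondary Endpoints section names complications, late failure rates and total antibiotic cost.

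**The concern.** There are two separate issues, and both concern the repeated laboratory panel.

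**Precision.** A two-group ANOVA is equivalent to a t-test. Applied to day-3 WBC or creatinine, it leaves in the error term all the variation that the patient's own enrolment value could explain. It also leaves the estimate exposed to chance imbalance at enrolment. The covariate is already being collected, so this loss is avoidable.

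**Timing.** The measurement tied to the end of treatment is described as coming after resolution. Patients reach that point at different times, or not at all, depending on how they respond. For WBC this is partly circular, because a WBC back in the normal range is one of the conditions for stopping treatment. A difference between arms at that visit is then hard to interpret.

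What is at stake is the reading of supportive efficacy and safety data. The Background section states the aim in terms of both efficacy and safety, and these are the repeated laboratory measures that bear on them.

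**Working it through.** **1. The plan's own figure.** Inputs from Statistics: failure 30% against 10%, 95% confidence, 80% power, 71 per group. The two-sided formula without continuity correction gives

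n = [1.96·√(2·0.2·0.8) + 0.8416·√(0.3·0.7 + 0.1·0.9)]² / 0.2² = (1.109 + 0.461)² / 0.04 = 61.6, so 62.

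With continuity correction: (61.6/4)·[1 + √(1 + 4/(61.6·0.2))]² = 71.2, or 72 when rounded up. The stated 71 is therefore reproduced to within rounding. It rests on the binary endpoint alone, so nothing below changes it.

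**2. Precision at day 3.** The document gives 71 per group. It gives no correlation, SD or target difference for any laboratory value, so r and the 0.4 SD difference below are assumptions. I also assume that the enrolment sample is drawn before the first dose.

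- Residual variance under ANCOVA, relative to ANOVA: 1 − r²
- Inflation from not adjusting: 1/(1 − r²)
- Standard error in SD units: √[(2/71)(1 − r²)], which is 0.168 at r = 0
- Difference detectable with 80% power: (1.96 + 0.8416) × standard error
- Power at 0.4 SD: Φ(0.4/standard error − 1.96)

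| r (assumed) | 1 − r² | 1/(1 − r²) | ANOVA group size matching ANCOVA with 71 | Detectable difference (SD) | Power at 0.4 SD |
|---|---|---|---|---|---|
| 0 (ANOVA) | 1.00 | 1.00 | 71 | 0.470 | 66% |
| 0.2 | 0.96 | 1.04 | 74 | 0.461 | 68% |
| 0.3 | 0.91 | 1.10 | 78 | 0.449 | 70% |
| 0.5 | 0.75 | 1.33 | 95 | 0.407 | 79% |
| 0.7 | 0.51 | 1.96 | 139 | 0.336 | 92% |

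At r = 0.3, 0.5 and 0.7, leaving out the enrolment value costs the equivalent of about 7, 24 and 68 patients per group for this comparison.

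**3. The resolution-timed visit.** Set side by side, the sections say that one measurement follows resolution, that some patients are expected not to improve, to progress or to die, and that all randomized patients are analysed. No visit is clearly defined for patients who die or do not resolve.

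To gauge the possible size, suppose that every patient classed as a failure lacks this visit. The planning rates then leave

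- Ampicillin-sulbactam: 71 × (1 − 0.30) = 49.7, about 50 of 71
- Ertapenem: 71 × (1 − 0.10) = 63.9, about 64 of 71

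As an illustration only, let severity be normal with SD 1 and let failure mean exceeding a common cut-off. Rates of 30% and 10% then imply arm means 0.757 apart. Among resolved patients the mean falls by 0.497 in the ampicillin-sulbactam arm (density 0.348 over 0.70) and by 0.195 in the ertapenem arm (density 0.175 over 0.90). The remaining difference is 0.757 + 0.195 − 0.497 = 0.455, about 60% of the full one. Under that model, selection shrinks a real difference.

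**The case against.** The strongest reply is that no laboratory value is an endpoint. Efficacy is judged by a blinded success/failure classification, and safety through adverse events and complications. The Statistics section does not say that WBC or creatinine will be tested between arms at any particular visit. The only clearly continuous named endpoint is total cost, which has no enrolment value. Covariates for supportive data may also be named in an analysis plan that is not shown. All of this stands, and it confines the point to supportive measures. It does not remove the point, because the article does commit the study's continuous data to a two-group ANOVA without a covariate.

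The size of the gain is also hypothetical. Surgery falls between enrolment and day 3 and may weaken the correlation; at r = 0.2 the inflation is only 1.04.

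A reader might infer that the resolution-timed visit sees only recovered patients. The text does not establish that. The visit is also tied to the end of treatment, which patients who fail may reach, and additional measurements are allowed. Nothing says that unresolved patients go unmeasured. What the text does support is that the visit time depends on outcome and that no visit is clearly defined for those who die or do not resolve. Creatinine and WBC are also measured on day 3 and at follow-up, so this visit is not the only look at safety.

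A reader might also conclude that ANOVA should be replaced throughout. That would leave total cost, liver function and electrolytes without a workable method, since none of them has a stated enrolment value.

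**Conclusion.** The point holds for the repeated laboratory panel and no further. At day 3 the unadjusted comparison of randomized groups is inefficient. It would be wrong to call it biased. Its variance is larger than necessary by a factor of 1.10 to 1.96 for r between 0.3 and 0.7, and by less if r is lower. Both r and the 0.4 SD used for the power figures are assumptions.

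The resolution-timed measurement is a separate weakness that covariate adjustment would not cure. A between-arm test there may compare selected groups of unequal size. The figures of 50 and 64 apply only if all patients who fail lack the visit, which the document does not say.

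A reader might take this as a threat to the main result. It is not: the failure-rate comparison uses the chi-squared or Fisher test, and the sample size is derived from that comparison.

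**What to change.** In the Statistics section:

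- Keep ANOVA for continuous data without an enrolment value, such as total cost.
- For WBC, platelets, glucose, BUN and creatinine, compare day-3 values between arms by ANCOVA with the enrolment value and the appendicitis/other stratum as covariates, log-transforming where the distribution is skewed.
- Report the values taken after resolution descriptively by arm, without a between-arm test. State how many patients contribute and how those who died or did not resolve are counted.

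This costs two or three sentences of analysis wording. It needs no new data, visits or patients and leaves the primary analysis as it is.
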